### Data analysis

Statistical programs SPSS 26.0 and Stata 15.1 for Windows will be used. The primary objectives of this study will be carried out through cox regression models. In addition, repeated measures ANOVA will also be performed to assess whether there is a time effect on the primary measures (treatment dropout and/or relapse) as well as secondary (craving, psychopathological state, recent cocaine use emotion regulation scores, trait impulsivity, other addictive behaviors) measures. In addition, these scores will be compared between the two treatment groups using a mixed model of repeated measures. All statistical tests will be two-tailed and will be considered significant if p <0.05. Also, for the characterization of the differences between men and women group comparisons will be conducted by means of chi-square tests (categorical variables) and *t*-tests (continuous variables). Finally, generalized linear models will be implemented to assess the psychopathological factors associated with treatment response. The need for the analyses to be adjusted for potential confounding variables that could introduce a bias in the results will be considered (e.g.,: age, psychopathology, among others). Especially if the study groups present an imbalance with confounding variables reported in previous literature.

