### Sample size calculation

Accepting an alpha risk of 0.05 and a beta risk of 0.2 in a two-sided test, 37 subjects are necessary in each treatment arm to recognize as statistically significant a minimum difference of 2.1 points on treatment relapse (i.e.,: Number of positive urine specimens submitted; primary outcome) between the two groups. The common deviation is assumed to be 3.1. It has been anticipated a drop-out rate of 5%. The parameters implemented to estimate the sample size are based on previous studies with similar populations (19).

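### The trial is powered on a mean count of positive urines, but the primary objectives are assigned to Cox regression with no relapse event defined, and repeated-measures ANOVA is assigned to dropout

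*Protocol article*

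**What the plan says.** Sample size calculation: for a two-sided alpha of 0.05 and 80% power, the article states that "37 subjects are necessary in each treatment arm". The effect behind that number is given as "a minimum difference of 2.1 points on treatment relapse (i.e.,: Number of positive urine specimens submitted; primary outcome) between the two groups", with an SD of 3.1 and an expected loss of 5%. No hazard ratio or number of events appears.

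Aims of the study and Instruments name two primary outcomes: dropout and relapse. Relapse is given by four measures: number of positive urines, percentage of negative screens, percentage of days abstinent, and self-reported frequency of use. Dropout is two missed appointments in a row with no answer by phone, checked weekly for 8 weeks and at follow-up. Urine is tested weekly over the same 8 weeks.

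Data analysis: "The primary objectives of this study will be carried out through cox regression models". It adds that "repeated measures ANOVA will also be performed to assess whether there is a time effect on the primary measures (treatment dropout and/or relapse") and on the secondary measures, and then that the scores will be compared between arms by a mixed model of repeated measures.

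**The concern.** A Cox model needs a time to an event. A total count, a percentage and a frequency are single values per patient with no event time, so Cox regression cannot be fitted to the powered variable as the article defines it. The reader therefore cannot tell which test decides the relapse question, and the 80% power does not describe the analysis named for it. Three methods (Cox, ANOVA, mixed model) could each be applied to some form of relapse. In an open-label trial, that choice should be fixed before the data are seen.

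The ANOVA sentence has a separate fault. Dropout happens at most once per patient. It is not a score measured again at each visit, so repeated-measures ANOVA is not a valid method for it.

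**Working it through.** **1. Reproducing the stated sample size.** Inputs from Sample size calculation: difference 2.1, SD 3.1, two-sided alpha 0.05, power 0.80, loss 5%.

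- n per arm = 2 × (1.960 + 0.842)² × 3.1² / 2.1² = 34.2, rounded up to 35.
- Allowing for loss: 35 / 0.95 = 36.8, rounded up to 37.

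This is the stated 37. With the t distribution the result is 36, then 36 / 0.95 = 37.9, rounded up to 38. A one-sided test would need 27 before loss, which does not match. The figure is sound, and it is a two-sample comparison of means.

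**2. What 74 patients give under Cox regression.** The documents give no hazard ratio or event count, so the number of events is assumed and shown as a range. Schoenfeld's formula with equal arms: detectable HR = exp(−2 × 2.8016 / √events).

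| Events | Detectable HR at 80% power |
|---|---|
| 37 (half of 74) | exp(−5.603 / 6.083) = 0.40 |
| 50 | 0.45 |
| 74 (all) | exp(−5.603 / 8.602) = 0.52 |

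A hazard ratio of 0.6 would need 121 events. With 74 events its power is 59%.

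**3. Is Cox better or worse than the count?** This cannot be settled from the documents, because the arm means are not given. As an illustration, I simulated 8 weekly samples, 37 per arm with no loss, a difference of 2.1 and SD 3.1. The beta-binomial model and the arm means are my assumptions. Time to first positive was tested by log-rank and the total count by t-test.

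| Mean positives, TAU / CBT4CBT | Log-rank power | t-test power |
|---|---|---|
| 6.0 / 3.9 | about 0.3 | about 0.8 |
| 5.05 / 2.95 | about 0.7 | about 0.8 |
| 4.5 / 2.4 | about 0.9 | about 0.8 |
| 4.0 / 1.9 | about 0.98 | about 0.8 |

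The ordering reverses within a plausible range of means. The stated 80% carries no information about a Cox analysis in either direction.

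**4. The ANOVA for the scores.** In its classical form, repeated-measures ANOVA uses only patients with a value at every visit. Table 2 collects craving (Weiss scale) and SCL-90-R at the end of treatment and at all three follow-ups, which is four assessments after allocation. If a share m is missing independently at each, (1 − m)⁴ remain: 0.9⁴ = 66% at 10% missing and 0.8⁴ = 41% at 20%. These rates are assumed. Scales not repeated at follow-up lose less.

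**The case against.** Four points can fairly be made for the plan.

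- Cox regression suits one of the two primary outcomes. Dropout is checked weekly, so time to dropout is a proper event time. It would be too much to say that Cox cannot analyse the primary measures. This stands.
- Relapse could be turned into an event, for example time to first positive weekly urine. That is true, but the article does not define it, and it would still not be the count on which the trial is sized.
- The mixed model of repeated measures is a between-arm comparison, can use incomplete data under a missing-at-random assumption, and may be meant to cover relapse. This stands in part: it is introduced as an addition, not as the primary test, and the 8-week total is one value per patient.
- The ANOVA is additional and is meant for time effects, not for the primary comparison of arms. This also stands, and makes the ANOVA the lesser part of the point. It does not make the method valid for dropout.

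A reader might also infer that relapse is censored at dropout and that the hazard ratio is therefore biased whenever retention differs. The article states no censoring rule, and such a rule may stand in a fuller document that is not shown. Nor does unequal retention alone bias a hazard ratio; leaving must also depend on relapse risk, given the covariates.

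**Conclusion.** The mismatch is real and lies within the article itself: the sample size rests on a difference in mean counts, while the primary objectives are assigned to Cox regression with no relapse event defined. The stated 80% power does not apply to that analysis. With 74 patients, Cox has 80% power only for hazard ratios of about 0.40 to 0.52, assuming that between half and all of them have an event.

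A reader might go further and say that Cox loses power against the count. The documents do not support this, because the direction depends on arm means that are not given. The invalid use of repeated-measures ANOVA for dropout is certain. The loss of patients from the ANOVA of scores is how the classical method behaves, not a rule in the protocol, and its size rests on assumed missing rates.

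**What to change.** Rewrite the paragraph under Data analysis as follows.

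1. Name a between-arm comparison of the mean number of positive weekly urines over the 8 weeks as the primary relapse analysis. This matches the sample size and leaves 37 per arm unchanged. State with it how missed samples are counted.
2. Keep Cox regression for time to dropout.
3. Use Cox for time to relapse only as a supporting analysis, with a defined event and a stated handling of dropout. One option is a sensitivity analysis that counts dropout as an event; this mixes the two primary outcomes, so it should not replace the main relapse result.
4. Delete the repeated-measures ANOVA and take time effects on the scores from the mixed model already planned.

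A mixed logistic model of the weekly urines is a tempting primary analysis, but it estimates an odds ratio, and the stated 80% power would not carry over to it either.

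The cost is one rewritten paragraph, with no new data and no change in sample size. Time to relapse becomes supportive.

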### Aims of the study

The aim of the present study is to evaluate whether adding a web-based cognitive behavioral therapy (CBT4CBT) to standard cocaine use disorder treatment improves treatment outcomes in a Spanish sample of patients with severe CUD (that require inpatient treatment). To do so, two primary outcomes are considered: (1) treatment retention (vs. dropout) and, (2) relapse (number of positive urine specimens submitted, percent negative urine screens, percent days of abstinence, self-reported frequency of cocaine use). As secondary outcomes the following variables are measured: craving, psychopathological symptoms, days of any drug use, CBT4CBT usability and treatment satisfaction.

The secondary objectives of the study are two-fold: (a) To explore differences between men and women in treatment response; (b) To explore if comorbid psychopathological symptoms, other addictive behaviors, craving and emotion regulation difficulties are predictive factors of treatment outcome at the end of inpatient treatment as well as at the end of the 8-week CBT4CBT + TAU or TAU and at follow-ups (1, 3, and 6 month).

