### Instruments

Primary outcome measures will be treatment dropout (two consecutive failures to attend and not answering the phone) and relapse (cocaine use: number of positive urine specimens submitted, percent negative urine screens, percent days of abstinence, self-reported frequency of cocaine use). Treatment dropout will be determined throughout the attendance at the appointments with the clinician (TAU or TAU + CBT4CBT), which will be carried out weekly during the 8-week period of treatment and at follow-up points. Relapse will be determined according to the participants' reports and throughout the presence of benzoylecgonine (metabolite of cocaine) in urine assessed with the Kinetic Microparticle Interaction test in a Solution (Roche Diagnostic System, Inc., Sommerville, NJ).

Secondary measures will cover sociodemographic variables and anthropometric measures (weight and high), cocaine craving, psychopathological symptoms and comorbidities, other addictive behaviors, personality traits, emotion regulation skills and CBT4CBT usability as well as treatment satisfaction.

Psychopathological symptoms and comorbid disorders will be assessed with a Clinical interview based on the DSM-5 diagnostic criteria for addictive behaviors, the MINI international neuropsychiatric interview (23), the Symptom CheckList-90 items-Revised (SCL-90-R) (24, 25), The State-Trait Anxiety Inventory (STAI) (26, 27) and the Beck's Depression Inventory (BDI) (28, 29). Craving and compulsive drug use will be measured with the following self-reported questionnaires: Severity of Dependence Scale (SDS) (30, 31), Cocaine Selective Severity Assessment (CSSA) (32, 33), Weiss Craving Scale (WCS) (34, 35). Other addictive behaviors will be measured, including gambling with the South Oaks Gambling Screen (SOGS) (36, 37), food with the Yale Food Addiction Scale 2 (YFAS) (38, 39), gaming with the DSM-5 criteria for internet gaming disorder (IGD) (40, 41) and sexuality with the Hypersexual Behavior Inventory (HBI) (42, 43).

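### Two primary outcomes, one of them four unranked measures, are all judged at p<0.05 with no success rule, so the false-positive rate can be about 10%, or higher if every measure is tested

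*Protocol article*

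**What the plan says.** In the protocol article, Aims of the study says that "two primary outcomes are considered: (1) treatment retention (vs. dropout) and, (2) relapse". Both that section and Instruments describe relapse by the same four measures: "number of positive urine specimens submitted, percent negative urine screens, percent days of abstinence, self-reported frequency of cocaine use". Neither section ranks them. With dropout, that makes five primary measures.

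Sample size calculation treats one of the five differently. It labels it "Number of positive urine specimens submitted; primary outcome" and bases the number of patients on it, "Accepting an alpha risk of 0.05 and a beta risk of 0.2 in a two-sided test".

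Data analysis states that "The primary objectives of this study will be carried out through cox regression models". It then adds repeated measures ANOVA on the primary and secondary measures and says that "these scores will be compared between the two treatment groups using a mixed model of repeated measures". The threshold is general: "All statistical tests will be two-tailed and will be considered significant if p <0.05". No section names an order of testing, a split of alpha, a combined endpoint or a requirement that both primary outcomes succeed.

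**The concern.** When several outcomes are primary, each is tested at 0.05, and nothing says how many must succeed, a reader may take any one significant result as proof of efficacy. The chance that at least one is significant when the treatment does nothing is then above 5%.

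The sample size section shows that the authors had a leading measure in mind, because it gives the urine count the whole 0.05. That is consistent with 5% overall only if the urine count is the sole primary endpoint or is tested first. The other sections place it as one of four relapse measures beside dropout. The trial's main claim therefore has no fixed decision rule, and the sections that bear on it do not agree.

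**Working it through.** **1. The plan's own figure.** Inputs from Sample size calculation: difference 2.1, common SD 3.1, two-sided alpha 0.05, power 80%, dropout 5%.

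n per arm = 2 × [3.1 × (1.960 + 0.842) / 2.1]² = 34.2, rounded up to 35. Allowing for dropout: 35 / 0.95 = 36.8, rounded up to 37. This reproduces the stated 37 per arm. The sample size is correct for one test at the full 0.05.

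**2. Two primary outcomes, either one sufficient.** This uses the article's own count of outcomes. For independent tests:

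1 − 0.95² = 0.0975, about 9.8%.

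Independence is the upper end here; positive correlation lowers the figure.

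**3. Five primary measures tested separately, any one sufficient.** For independent tests:

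1 − 0.95⁵ = 0.226, about 23%.

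The documents give no correlations, so a range is assumed. Simulation of five two-sided normal tests at 0.05 (1,000,000 draws) with one common correlation gives:

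| Assumed correlation | Chance of at least one false positive |
|---|---|
| 0 | 22.6% |
| 0.3 | 20.8% |
| 0.5 | 18.2% |
| 0.7 | 14.8% |
| 0.8 | 12.8% |
| 0.9 | 10.2% |
| 0.95 | 8.5% |

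A perhaps more realistic pattern has the four relapse measures correlated at 0.7 to 0.9 and dropout independent of them. It gives 17.4% down to 13.9%.

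**4. What splitting alpha would cost.** Power is for the urine count with 35 evaluable patients per arm.

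| Split | Alpha per test | Power | n per arm for 80% power | After 5% dropout |
|---|---|---|---|---|
| Two outcomes | 0.05 / 2 = 0.025 | 72% | 42 | 45 |
| Five measures | 0.05 / 5 = 0.01 | 60% | 51 | 54 |

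A fixed testing order needs no split. It keeps the urine count at 0.05 and the 37 per arm valid.

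**The case against.** The strongest reply is that the article counts two primary outcomes, not five. It sends the primary objectives to Cox regression, which suits dropout and relapse as two events and does not suit percentages or frequencies of use. Instruments can also be read as making one determination of relapse from urine and self-report together. Two of the measures come from the same specimens and are likely to be highly correlated. This stands in part. Separate tests of all five measures are an inference, supported by the mixed-model sentence but not stated measure by measure. It does not remove the problem, because two outcomes already give up to 9.8%.

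A second reply is that testing order is often left to a statistical analysis plan and that this is a condensed article. That would answer a silent text. This one states a threshold for all tests, and its sections differ on which measure is primary. A general 0.05 sentence does not exclude an adjustment described elsewhere, but none is named.

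A third is that both outcomes might have to succeed. That would control the error, but the article does not say so. It also gives no joint power, which cannot exceed the lower of the two separate powers.

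A reader might go further than the text allows in four ways:

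- **An unconditional 13% to 23%.** That range needs five separate tests, success on any one of them, and assumed correlations between 0.8 and 0.
- **Counting 20 tests.** Five measures at four time points would give 64% if independent (1 − 0.95²⁰). The planned Cox and repeated-measures models pool time points, and no separate test at each visit is planned.
- **Saying that no decisive measure is named anywhere.** The sample size section names one; the fault is that the other sections do not follow it.
- **Adding bias to the count.** Self-report in an open-label trial is a fair worry, but it is a separate issue and does not change these figures.

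**Conclusion.** The concern holds at a moderate size. The article names two primary outcomes, applies 0.05 to every test and gives no success rule, while its sample size assumes one primary measure at the full 0.05.

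If success on either outcome counts, the false-positive rate is up to about 9.8%, roughly twice the nominal level. If each of the five measures is tested, it is about 13% to 23% for assumed correlations of 0.8 down to 0, and about 8% to 10% for 0.95 to 0.9. Every figure assumes that one significant primary result is enough for a claim, which the article neither states nor excludes. The five-measure figures also rest on correlations that the documents do not supply. The sample size arithmetic itself is sound.

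**What to change.** Align Aims of the study, Instruments and Data analysis with the label already used in Sample size calculation:

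- **Primary endpoint:** the number of positive urine specimens, over the eight weeks of weekly testing, at two-sided 0.05. Sample size calculation gives no time window, so state it there too, and say which single model gives the primary p value.
- **Second in order:** treatment dropout, at two-sided 0.05, tested as confirmatory only if the first test is significant.
- **Secondary and supportive:** percent negative screens, percent days of abstinence, self-reported frequency of use, and all follow-up results.

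This holds the overall error for the two confirmatory tests at 5%, adds no patients and leaves 37 per arm valid. It is a change of wording only.

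There are two downsides. Dropout loses its independent claim to primary status, so an effect on retention without one on urine results could not be claimed as confirmatory. And a count of positive specimens submitted can fall because patients leave and submit fewer, so percent negative screens should be reported beside it as a supportive check.

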## Discussion

CBT4CBT is a CBT web-based treatment which concomitant to TAU has shown to improve current treatments in multiple US-based studies (18–20). However, up to date it has never been implemented in Spain.

This study aims to improve current evidence-based treatments for severe CUD (that requires inpatient treatment) through the implementation of a more intensive and extensive treatment which is grounded on a web-based CBT approach (CBT4CBT). Additionally, predictive factors for treatment outcome will be assessed. The main strength and contribution of this study will be the enhancement of CUD treatment, using a concomitant web-based treatment approach to TAU. CBT4CBT has the potential to optimize current treatments by facilitating daily access to it when needed. This study also explores different secondary measures (i.e., sociodemographic, cocaine use related variables, craving, personality traits, as well as comorbid psychopathology and other addictive behaviors) that can help to better understand predictive factors of treatment outcomes at two different clinical settings (i.e., inpatients treatment and day care treatment + CBT4CBT) and at 6 different time points (end of each treatment setting and at three different follow-up points−1, 3, and 6 months after treatment-). This can lead to the possibility of targeting specific characteristics in a population of severe CUD and to individualize treatments accordingly for aiming to a better outcome. Furthermore, this study will take into account a gender perspective and explore gender differences in predictive factors for treatment outcome and the efficacy of CBT4CBT.

The potential limitations of this study are the exclusion of patients with opioid use disorder or any other severe condition that can interfere in the participation or assessment of the study. Additionally, dropout rates are considered as treatment outcome although participants can dropout before starting CBT4CBT or TAU after arm allocation which would limit the power of the analysis. Finally, some patients will not be able to join the study if they live in a different area or attend to another treatment than day care. This is required for enabling the implementation of the full treatment and may be strength for homogeneity but it can also limit the generalization of results.

## Ethics statement

The study was approved by the Research Ethics Committee of the Hospital de la Santa Creu i Sant Pau, project number IIBSP-CBT4CBT-2020-1116. The study will be carried out in accordance with the Declaration of Helsinki and Good Clinical Practices ethical principles. All participants will be informed about the study and they will have to provide informed consent for participation before their inclusion. This study does not pose any risk to the participants. Central Clinical Research and Clinical Trials Unit of Research Institute of the Hospital de Sant Pau will monitor through periodic visits the correct progression of the project, notifying protocol deviations. They will be aware of every single step of the project.
